### Statistical analysis

The results will be presented as mean score plus or minus standard deviation and as percentages. Categorical data will be analyzed with Fisher’s exact test or the Mann-Whitney U test where appropriate. Continuous data will be analyzed with the Student’s t test or Pearson’s test where appropriate. Multi-ranked data will be analyzed using the Mann-Whitney U test. Differences will be considered statistically significant at *P* < 0.05 (two-tailed). All statistical analyses will be performed using the Statistical Package for the Social Sciences (version 13.0; SPSS; Chicago, Illinois, USA).

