### Study design

This study will be a single-center, randomized, placebo-controlled, parallel group, and patient-assessor-blinded clinical trial. After completing informed consent, 488 eligible patients will be recruited and randomized to one of eight groups: 10–15 cc left sided TH study group (*N* = 61) and a corresponding control group (*N* = 61), 10–15 cc right sided TH study group (*N* = 61) and a corresponding control group, 15–30 cc left sided TH study group (*N* = 61) and a corresponding control group (*N* = 61), and 15–30 cc right sided TH study group (*N* = 61) and a corresponding control group. The patients in each of the study groups will receive 36 sessions of Chinese acupuncture in addition to standard treatments for TH, which include anticonvulsant therapy, antihypertensives, osmotic diuretics for the management of intracranial pressure, and invasive treatments as necessary. The patients in each of the control groups will receive standard treatments only. Patients’ neurologic status will be assessed at baseline and at the end of treatment as well as at 30 day and 90 day follow-up intervals. CT imaging will be performed on admission and at 90 days follow up. All patients will be required to complete written informed consent prior to enrollment. If patients are unable to complete written informed consent, it will be obtained from their relatives. A flow chart demonstrating an outline of the study is included in Fig. 1.

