### Procedure

Eligible patients will be randomized to either study groups (acupuncture plus conventional treatment) or control groups (conventional treatment alone) based on the size and side of their TH. After successful randomization, neurological assessments will occur at four time points: before treatment sessions begin, 30 days after onset of TH, at the end of treatment (6 weeks), and 90 days after onset of TH.

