### Sample size calculation

Using the variable NIHSS score, the primary outcome measure of the study, PS Power and Sample Size software (version 3.0) was used to determine an appropriate sample size for the study. In a previous study, NIHSS scores in each subject group exhibited a normal distribution with a standard deviation of 4.2 points [11]. This assumes a difference of 2.3 points between the groups, as shown in a previous study on moderate TH. A sample size of 488 provides 80% power (α = 0.05) to detect a beneficial effect of early acupuncture therapy on the primary outcome, assuming a 10% non-adherence to treatment and a 3% loss to follow-up.

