Another potentially confounding factor is the involvement of adjacent brain tissue as a secondary result of the initial thalamic insult. Adjacent brain tissue can necrose either directly via extension of the thalamic bleed or indirectly via mass effect from the thalamic bleed and/or edema related to the thalamic bleed. Areas at specifically high risk include the genu of the internal capsule which lies lateral to the thalamus, the posterior limb of the internal capsule which lies posterolateral to the thalamus, the anterior limb of the internal capsule which lies anterolateral to the thalamus, and the peri-thalamic/peri-ventricular white matter which lies superior to the thalamus. Involvement of the genu of the internal capsule, the posterior limb of the internal capsule, and adjacent white matter could result in paralysis. Involvement of the posterior limb of the internal capsule could also result in sensory loss or impaired comprehension [36]. Finally, involvement of the anterior limb of the internal capsule could result in cognitive issues. Involvement of any of these areas could potentially impact how a patient recovers and/or sway the post-stroke assessment scores in one direction or another depending on how many of the affected patients ended up in the control group or the intervention group. To combat this, we utilized two mechanisms. First, we excluded patients from the study whose TH on admission CT demonstrated extension of the insult beyond the thalamus. However, admission CT often does not disclose the true area affected by the insult. CT performed 90 days later is much more sensitive in demonstrating the insult’s true encompassment. We therefore further subdivided the groups by size. While all subjects in the study have moderate thalamic hemorrhage, groups were further subdivided into subjects with 10–15 cc of TH and 15–30 cc of TH. Patients with 10–15 cc of TH are much less likely to experience insults to brain tissue external to the thalamus than patients with 15–30 cc of TH as a result of the smaller size of the initial bleed. We also plan to retrospectively analyze the results of CT scans performed 90 days following the insult to determine what percent of patients in each group experienced extension of their primary insult to tissue beyond the thalamus and how this may have affected the results in that group. After dividing patients by side of hemorrhage and size of hemorrhage four intervention groups were established, and along with the corresponding four control groups, this totaled eight distinct subject groups.

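### The primary NIHSS comparison is an unadjusted t test although baseline NIHSS is measured in every patient, which costs precision; that baseline is scheduled after randomisation, at a time point controls do not have.

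*Protocol article*

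**What the plan says.** **Test.** The Statistical analysis section states: "Continuous data will be analyzed with the Student’s t test or Pearson’s test where appropriate". Fisher's exact and Mann-Whitney tests are named for other data types. None of these takes a covariate.

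**Baseline data.** The Study design section says that patients' "neurologic status will be assessed at baseline and at the end of treatment as well as at 30 day and 90 day follow-up intervals", so a baseline NIHSS will exist for all patients.

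**Outcome.** The Abstract makes the primary outcome the change in NIHSS at 30 and 90 days. The Primary outcome measure section makes it the NIHSS score at end of treatment, 30 days and 90 days.

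**Timing of baseline.** The Procedure section reads: "After successful randomization, neurological assessments will occur at four time points: before treatment sessions begin". The Subject enrollment section lists what is collected before enrolment. NIHSS is not named there, though the list is open-ended.

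**Comparison units.** The Discussion says: "After dividing patients by side of hemorrhage and size of hemorrhage four intervention groups were established", each with its own control group. The Aims section says that study and control groups formed by size and side will be compared.

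**Sizing.** The Sample size calculation section says that "NIHSS scores in each subject group exhibited a normal distribution with a standard deviation of 4.2 points" and "This assumes a difference of 2.3 points between the groups".

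**The concern.** Baseline severity usually predicts later NIHSS. A two-sample t test on the follow-up score makes no use of it. A t test on change uses it with a fixed coefficient of one, which is inefficient unless baseline and follow-up are very highly correlated. Either way the interval is wider than it need be. On the score, any chance baseline imbalance also stays in the estimate.

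The randomisation does not remove that imbalance. The Randomization and blinding section says stratified blocks will not be used, while the Discussion says they will be, by sex and age. Neither version balances baseline NIHSS.

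The baseline measurement has a weakness of its own. It follows randomisation and is anchored to the start of treatment sessions. Controls have no sessions, so the time point is undefined for them and may fall at a different moment in the first days after the bleed. Controls receive no sham, so patients may know their arm when examined, and several NIHSS items depend on the patient's response. This affects any analysis that uses baseline, whether change or ANCOVA.

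Pearson's test is also listed as an option for continuous data. Pearson correlation does not compare two groups, and Pearson's chi-square is for categorical data.

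**Working it through.** **Inputs from the article:** SD of NIHSS scores 4.2; difference 2.3; two-sided α 0.05; power 80%; 10% non-adherence and 3% loss to follow-up; eight groups of 61.

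**Assumptions, not in the article:** correlation r between baseline and follow-up NIHSS, shown at 0.3, 0.5 and 0.7; the same SD of 4.2 at baseline and follow-up.

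**Step 1. Reproduce 488.** Per group, n = 2 × [4.2 × (1.960 + 0.842) / 2.3]² = 52.3, rounded up to 53. Inflated by 13%: 53 / 0.87 = 60.9, so 61. Dividing by 0.90 and then 0.97 also gives 61. Then 8 × 61 = 488, an exact match. (With the t distribution, n is 54 per group and the total 496 to 504.) The calculation is an unadjusted two-sample comparison within one size-by-side pair.

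**Step 2. Effective SD under each analysis.**
- t test on score: 4.2
- t test on change: 4.2 × √[2(1 − r)]
- ANCOVA on baseline: 4.2 × √(1 − r²)

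**Step 3. Power with 53 per group.** Power = Φ(2.3 / [SD × √(2/53)] − 1.960). For the score: 2.3 / (4.2 × 0.1943) = 2.82, so Φ(0.86) = 80.5%.

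| r (assumed) | t test on score | t test on change (SD) | ANCOVA (SD) |
|---|---|---|---|
| 0.3 | 80.5% | 66.4% (4.97) | 84.0% (4.01) |
| 0.5 | 80.5% | 80.5% (4.20) | 90.2% (3.64) |
| 0.7 | 80.5% | 95.3% (3.25) | 97.7% (3.00) |

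**Step 4. Evaluable patients per group for 80% power** at r = 0.3, 0.5, 0.7: score 53 throughout; change 74, 53, 32; ANCOVA 48, 40, 27. Against the score, ANCOVA needs 9% fewer at r = 0.3 (1 − 48/53) and 49% fewer at r = 0.7 (1 − 27/53). The variance of change relative to ANCOVA is 2(1 − r)/(1 − r²) = 2/(1 + r), that is 1.54, 1.33 and 1.18.

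**Step 5. Chance imbalance.** With 61 v 61, the baseline difference has standard error 4.2 × √(2/61) = 0.76. Its 95% range is about ±1.5 points, or 65% of the 2.3-point target (1.49/2.3).

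**Step 6. Pooling.** If the four pairs were pooled (4 × 53 = 212 evaluable per arm), power for 2.3 points exceeds 99.9% with or without stratum adjustment.

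**The case against.** **The t test is valid.** Under randomisation it is unbiased with correct error rates, and the sample size was built on it. This stands. Nothing here makes 488 wrong, and adjustment is a gain in efficiency.

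**The gain is assumed, and may be small.** This also stands. At r = 0.3, ANCOVA adds only 3.5 points over the t test on the score. At r = 0.7, it adds only 2.4 points over the t test on change. The change score falls below the planned 80% only if r is under 0.5.

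**A condensed article may leave covariates to an analysis plan.** Partly. A list of covariates could be elsewhere, but this article names the test, and the test it names has no covariate.

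**A reader might infer that the plan ignores the size and side strata, so its standard errors are too large.** The documents do not support that. The Aims and Discussion describe comparisons within size-by-side pairs, and 488 reproduces from a within-pair calculation. A t test inside a pair already conditions on both factors. The inference would apply only to a pooled test, which the article does not describe.

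**A reader might infer that the assessor knows the allocation at baseline.** The documents do not say so. The Abstract and Study design section declare assessor blinding, and the Discussion says the outcomes reviewer is blinded. What remains is patients who may know their arm and timing that may differ. If the unadjusted follow-up score is analysed, a distorted baseline cannot bias the comparison at all.

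**Pearson's test is qualified by appropriateness and may mean correlation.** Possible, and the wording should then say so.

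**Conclusion.** The point holds as one of precision. The stated primary analysis leaves out a baseline value that is already collected, or merely subtracts it, and the article does not settle which because the Abstract and Methods differ. Over assumed correlations of 0.3 to 0.7 with equal SDs, ANCOVA raises within-pair power from about 80% to between 84% and 98% relative to the score, and is better than change throughout that range. The exact gain cannot be known from the article.

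It would be too strong to say that the baseline is ignored outright, since the Abstract's change score does use it. The baseline timing is a real but limited weakness: it is set after randomisation and tied to an event controls lack. It matters for change and for ANCOVA, so it should be corrected together with the analysis. The change is advisable; the trial is not invalid without it.

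**What to change.** 1. Reconcile the Abstract with the Primary outcome measure section, so that there is one primary NIHSS endpoint.
2. In the Statistical analysis section, state that this endpoint is analysed by ANCOVA with baseline NIHSS as covariate within each size-by-side pair. If the pairs are pooled, add side and volume stratum as covariates.
3. In the Procedure section, state that baseline NIHSS is recorded in both arms before the allocation envelope is opened.
4. Remove Pearson's test as a two-group test for continuous outcomes, or restrict it to correlation.

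The cost is a few sentences and a slightly earlier baseline examination. No additional patients or measurements are needed.

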## Discussion

In this randomized controlled trial, we will observe the effect of acupuncture therapy on patients with acute TH. The findings of this project are expected to provide evidence for the efficacy of acupuncture in improving the prognosis of patients with moderate TH. To minimize bias, stratified block randomization will be used according to sex and age, and the outcomes reviewer will be blinded. Subjects will be treated alone in a treatment room in order to avoid any communication with other subjects.

Generally speaking, no ideal placebo-controlled acupuncture trials have been performed previously [34]. Because recent acupuncture trials have examined so-called sham acupuncture techniques, including: needling of acupuncture points through non-penetrating needles, needling of non-acupuncture points, and needling of acupuncture points that are not indicated for that specific condition, these prior trials have not accurately reflected TCM theory and therefore have not properly assessed it [34]. Further complicating things is that sham acupuncture has been shown to have some efficacy [35]. In China, many patients and their families have had acupuncture at some time in their lives or are at least familiar with the acupuncture process. Therefore, it would be difficult to design a trial assessing the utility of sham acupuncture versus real acupuncture while keeping the patient blinded.

The decision was made to examine patients with left sided TH separately from patients with right sided TH. In the majority of patients, Broca’s cortical area and Wernicke’s cortical area are located in the left hemisphere. Therefore, patients with left hemisphere stroke (ischemic or hemorrhagic) are at risk for language deficits. Similarly, patients with right sided insults are at risk for symptoms of visual neglect. Both language deficits and visual neglect can have a profound impact on the way a patient responds to treatment and rehabilitation of other neurologic deficits. Therefore, to account for the potentially confounding effects of language deficits and visual neglect respectively, patients were subdivided into right and left TH subgroups.

Along the same lines, not all patients have their language centers located in their left hemisphere. While the majority of left handed patients have their language centers in the left hemisphere, some do have them in the right hemisphere. Therefore, in this study, we have only included right handed patients.

Another potentially confounding factor is the involvement of adjacent brain tissue as a secondary result of the initial thalamic insult. Adjacent brain tissue can necrose either directly via extension of the thalamic bleed or indirectly via mass effect from the thalamic bleed and/or edema related to the thalamic bleed. Areas at specifically high risk include the genu of the internal capsule which lies lateral to the thalamus, the posterior limb of the internal capsule which lies posterolateral to the thalamus, the anterior limb of the internal capsule which lies anterolateral to the thalamus, and the peri-thalamic/peri-ventricular white matter which lies superior to the thalamus. Involvement of the genu of the internal capsule, the posterior limb of the internal capsule, and adjacent white matter could result in paralysis. Involvement of the posterior limb of the internal capsule could also result in sensory loss or impaired comprehension [36]. Finally, involvement of the anterior limb of the internal capsule could result in cognitive issues. Involvement of any of these areas could potentially impact how a patient recovers and/or sway the post-stroke assessment scores in one direction or another depending on how many of the affected patients ended up in the control group or the intervention group. To combat this, we utilized two mechanisms. First, we excluded patients from the study whose TH on admission CT demonstrated extension of the insult beyond the thalamus. However, admission CT often does not disclose the true area affected by the insult. CT performed 90 days later is much more sensitive in demonstrating the insult’s true encompassment. We therefore further subdivided the groups by size. While all subjects in the study have moderate thalamic hemorrhage, groups were further subdivided into subjects with 10–15 cc of TH and 15–30 cc of TH. Patients with 10–15 cc of TH are much less likely to experience insults to brain tissue external to the thalamus than patients with 15–30 cc of TH as a result of the smaller size of the initial bleed. We also plan to retrospectively analyze the results of CT scans performed 90 days following the insult to determine what percent of patients in each group experienced extension of their primary insult to tissue beyond the thalamus and how this may have affected the results in that group. After dividing patients by side of hemorrhage and size of hemorrhage four intervention groups were established, and along with the corresponding four control groups, this totaled eight distinct subject groups.

Previous research has demonstrated that patients with hand paresis only following stroke may not only be the most likely to benefit from acupuncture therapy but also the most likely to experience complete resolution of their neurologic symptoms [37]. As a result, it is important, if able, to determine the results of our intervention in patients with hand paresis only. As only patients with moderate thalamic hemorrhage will be enrolled in this trial, it is unlikely that our study will include many, if any, subjects with hand paresis only. However, if there are subjects with hand paresis, the results of our intervention will be analyzed retrospectively following conclusion of the trial.

The primary outcome measure is NIHSS result. While the NIHSS is a fine test, its comprehensiveness is somewhat lacking. In fact, previous studies examining interventions in stroke patients may have failed due to their sole reliance on the NIHSS as an outcome measure [38]. Therefore, additional tests measuring paralysis, language, visual neglect, and stroke outcome were also included in this study.

Under strict quality control, this trial will attempt to answer the question of whether or not acupuncture can improve neurologic outcome following moderate TH.

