## Methods/Design

### Aims

We hypothesize that the addition of acupuncture to conventional treatments will improve neurological prognosis in TH patients. To test this hypothesis, we will compare study and control groups created based on the size and side of the TH. The study groups will receive acupuncture in addition to standard treatments, while the control groups will receive standard treatments alone.

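### The trial asks one question but sets up four separate side-by-size comparisons; with the same true effect in every group, their results would disagree in about 59% of trials

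*Protocol article*

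**What the plan says.** The hypothesis under Aims is general: adding acupuncture improves neurological prognosis in these patients. The closing Discussion also poses one overall question. The test described under Aims is a set of group comparisons: "we will compare study and control groups created based on the size and side of the TH". Under Study design, each study group of 61 has its own corresponding control group, and "488 eligible patients will be recruited and randomized to one of eight groups".

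The Discussion adds: "The decision was made to examine patients with left sided TH separately from patients with right sided TH". Its reason is that language deficits and visual neglect "can have a profound impact on the way a patient responds to treatment"; the text then calls these effects confounding. The split at 15 cc is given a similar purpose, also under the label of confounding.

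The Sample size calculation states: "A sample size of 488 provides 80% power (α = 0.05) to detect a beneficial effect of early acupuncture therapy on the primary outcome". The Statistical analysis section lists Fisher's exact, Mann-Whitney, Student's t and Pearson's tests, read at two-tailed P < 0.05. It does not say how results from four pairs become one answer.

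**The concern.** Taken together, these places describe four study-versus-control tests of the same outcome, each with its own control group and its own 80% power. Four such tests will often disagree by chance even when the effect is identical everywhere. The trial would then report, say, three significant groups and one not, with no stated way to turn that into an answer to its single question. A reader would be tempted to explain the odd group by its side or size, which a difference in P values cannot support.

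The stated reason for the split does not call for separate tests either. Within a pair allocated 1:1, side and size cannot confound the arm comparison. If the aim is to remove prognostic variation due to side and size, putting both in one model does that and keeps all the patients in one comparison.

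**Working it through.** **Inputs.** SD 4.2, difference 2.3, 80% power, 10% non-adherence and 3% loss to follow-up (Sample size calculation); two-sided 0.05 (Statistical analysis); 61 per arm in four pairs (Study design). All calculations are for one outcome at one time point.

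**Reproducing 488.** Per arm, n = 2 × [4.2 × (1.960 + 0.842) / 2.3]² = 52.3, so 53. Inflating for losses: 53 / 0.87 = 60.9, so 61; applying the two losses in sequence, 53 / (0.90 × 0.97) = 60.7, also 61. Then 8 × 61 = 488, exactly the stated total. One pooled comparison would need 2 × 53 = 106, or 2 × 61 = 122 after losses. The stated 80% is therefore the power of one side-by-size pair.

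**Chance of a mixed result with the same 2.3-point effect in all four pairs, at 80% power each.**

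| Pairs significant | Formula | Probability |
|---|---|---|
| 4 | 0.8⁴ | 41.0% |
| 3 | 4 × 0.8³ × 0.2 | 41.0% |
| 2 | 6 × 0.8² × 0.2² | 15.4% |
| 1 | 4 × 0.8 × 0.2³ | 2.6% |
| 0 | 0.2⁴ | 0.2% |

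Mixed = 1 − 0.8⁴ − 0.2⁴ = 58.9%. With 53 evaluable per arm and t tests, power per pair is 79.8% and the figure is 59.4%; a simulation of t tests gave 59.6%.

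**Range.**
- All 61 per arm evaluable: power 85% to 86%, mixed 46% to 48%.
- 59 per arm analysed (61 × 0.97), effect diluted by 10% non-adherence to 2.07 points: power 76%, mixed about 67%.

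**What the mixtures look like.** Both left pairs significant and neither right pair: 0.8² × 0.2² = 2.6%. The reverse, and the two size patterns, have the same probability, so clean splits total 4 × 2.56% = 10.2% of trials.

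**One model instead.** Four pairs at 53 per arm give 212 per arm. The standard error of the overall effect is 4.2 × √(2/212) = 0.41, so power for 2.3 points exceeds 99.9%.

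**Interaction tests.** For treatment by side (or by size), with 106 per arm at each level, the standard error is 4.2 × √(4/106) = 0.82. Power for a difference in effect of 2.3 points is Φ(2.3/0.816 − 1.96) = 80%; for 1.15 points it is Φ(1.15/0.816 − 1.96) = 29%. Each test has a 5% false-positive rate; for the two together the chance of at least one is about 1 − 0.95² = 9.8%.

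**The case against.** The strongest reply has four parts.

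*No sentence gives each pair its own verdict.* This is correct. It is inferred from Aims, from the corresponding control groups, from the separate examination of left and right, and from a sample size that works only per pair. If the size groups were pooled within each side, each side would have 97.9% power and the two sides would disagree in only 2 × 0.979 × 0.021 = about 4% of trials. The per-pair sample size points to four comparisons, not two.

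*The split is for confounding, not to study different responses.* This also stands. A reader might infer, from the remark about how patients respond to treatment, that the trial set out to ask whether the effect differs by side and then left that untested. The documents do not support this: the Discussion labels the reason confounding, and no aim or outcome asks whether the effect differs by side or size.

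*No text proposes to read discordant P values as different effects.* Correct. The plan to consider "how this may have affected the results in that group" concerns extension beyond the thalamus on the 90-day CT within a group, not a comparison of effects across groups. A reader might also take the 59% as the chance of a result such as left but not right; such clean patterns make up about 10%, and the commonest mixture is three of four.

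*An interaction test may be in an analysis plan that is not shown.* It may, and its absence from the article is not the point. The point is the separate-comparison structure that the article does fix, and that one model answers the stated question better.

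**Conclusion.** The point holds in a limited form. The protocol asks one question and is built as four separately powered comparisons with simple tests. With an equal true effect of 2.3 points, the four results would be mixed in about 59% of trials (range about 46% to 67%). That mixture would say nothing about whether the effect varies by side or size. The figure assumes four independent pairs, one outcome at one time point, the protocol's SD and difference, and the inference that each pair is tested on its own.

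The phrase about randomizing to eight groups might suggest that side and size are randomized. Randomization and blinding already describes 1:1 allocation to two treatments within size and side, so this needs only a minor clarification.

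**What to change.** - Make the primary analysis one model of all patients with arm, side and size, giving one overall treatment effect, confidence interval and test.
- Report the four group effects as differences with 95% confidence intervals and no separate verdicts.
- Prespecify treatment-by-side and treatment-by-size tests, and claim that the effect differs by side or size only from these. State their limits: about 80% power for a 2.3-point difference in effect, about 29% for 1.15 points, and a separate 5% error rate each.
- Reword the allocation sentence to say that patients are randomized to two arms within four side-and-size groups.

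The cost is wording and analysis code only; no patients or data are added. The trade-off is that a claim about one group alone would no longer follow from a single P value in that group.
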